**Methods:**

MIMICH is a randomised control trial (RCT) comparing routine treatment for diabetes, the standard of care, to withholding metformin (the intervention) during pregnancy, in women with type 2 diabetes or gestational diabetes (GDM) who have maternal or uteroplacental risk factors for placental disease in a target sample of 225 participants. Participants receive the recommended schedule of antenatal care, including serial biometry ultrasound with the addition of fractional thigh volume measurement. The primary outcome will be change in estimated weight z-score from second trimester to birth. The MIMICH II study will follow up the mothers and infants at 3–6 months and 12–15 months after pregnancy. Study procedures include anthropometric measurements from both mother and baby, data collection about medications, complications after birth and feeding, and maternal blood sampling. Infant echocardiography, blood pressure measurements and venepuncture will also be undertaken where possible.

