## Methods: participants, interventions and outcomes

### Trial setting {9}

The study is conducted within Manchester University NHS Foundation Trust (MFT) (single Hospital Trust). Women will initially be identified in antenatal clinics at three hospital sites within MFT (St Mary’s Oxford Rd, St Mary’s Wythenshawe, North Manchester General Hospital) and provided with information regarding the study. Confirmation of eligibility, consent and all study visits will take place within the Maternal & Fetal Health Research Centre, St Mary’s Oxford Rd. Pregnancy outcome data will be collected following review of clinical records by study midwives within MFHRC with assistance from CRN research staff at each of the identification hospital sites. Participation in the postnatal follow-up study will be offered to participants who consent to be contacted about future research. All procedures including screening, consent and study visits will take place at St Mary’s Hospital MFT by a delegated member of the research team.

Participants will continue to receive the standard pathway of care throughout the course of the trial, with the exception of the omission of metformin therapy for those participants randomised to the intervention arm.

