#### Outcomes for MIMICH II

Primary infant outcome: Difference in the delta (birth to visit 2) weight SD score between infants following maternal treatment with or without metformin

Infant secondary outcomes:Metabolic health indices including biochemical (insulin, glucose, lipid profile, leptin, adiponectin)Anthropometric measurements (crown-rump, crown-heel lengths; weight; arm, thigh, head, abdominal circumferences; biceps, triceps, subscapular skinfold thicknesses) expressed as z-scores using WHO charts where applicableCardiac measurements including systolic and diastolic blood pressure and echocardiogram (left ventricular dimensions, diastolic function and systolic function)Transcriptomics and metabolomics are collected from infant and mother and differentially expressed genes and metabolites will be determined between metformin-exposed and non-exposed infants

Maternal secondary outcomes: Postnatal weight change (from booking to late pregnancy), adiposity (waist:hip ratio, biceps, triceps, subscapular skinfold thicknesses), cardiometabolic health measurements (insulin resistance, lipids, hsCRP, inflammatory cytokines, BP)

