### Sample size considerations {14}

The primary outcome is a change in foetal growth velocity in the third trimester. Our group has pioneered the use of volumetric ultrasound techniques to improve the detection of foetal growth abnormalities [47, 48]. Previous studies investigating hypoglycaemic agents in pregnancy have used birthweight as the primary outcome, which provides only a crude estimate of foetal growth. In pregnancies where there are conflicting exposures influencing foetal growth and placental function (e.g. hypertension and hyperglycaemia), absolute birthweight is not sufficient to detect subtle, but clinically significant changes in foetal growth and placental function. To address this limitation, in this study, longitudinal measures of foetal growth will be used to quantify the deviation in foetal growth in the third trimester. This will be derived from the delta z-score in estimated foetal weight (using the modified EFW TVol formula [44]) over the third trimester using WHO foetal growth charts [43]. This will provide a more sensitive assessment of the effect of metformin on foetal growth than birthweight alone; the use of a continuous measure as a primary outcome also makes the study more efficient as it requires a smaller sample size. In order to verify the primary outcome, the eCRF will capture the TVol measurement and the EFW at each scan as well as recording the 2nd trimester and 3rd trimester deviation scores. The source data (scan report) will verify the 2D biometry.

In a comparison of women with type 2 diabetes treated with metformin recruited to the VELOCITY study, the mean delta z-score between the second trimester and birth was − 0.51 (SD 1.1) for women with a placental disease risk factor (*n* = 34) and 0.30 (SD 0.9) in women without a risk factor (*n* = 45). A sample size of 190 women (95 in each group) will provide 80% power to detect a clinically significant difference in delta z-scores of 0.41 (SD 1.0) between the treatment groups; this difference would reflect a rightward shift in the birthweight distribution in women in whom metformin was withheld to a mean of − 0.1.

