The primary outcome for the postnatal follow-up study will be weight gain trajectory, determined as change in weight z-score, between birth and 12 months of age. Assuming a population z-score weight gain of 0.08–0.12 (SD 0.9) [37, 38] at 3–6 and 12 months, *n* = 39 (*β* = 0.8) or *n* = 70 (*β* = 0.9) per group will be required to show a 0.5 difference in z-score between groups (retention 35–63%). Excessive infant weight gain (> 0.67 SD, representative of the width of each percentile band on standard growth charts (e.g. 2nd–9th, 9th–25th percentile [8]) in the first year of life is strongly associated with an adverse adult cardiometabolic risk profile [36, 37]. Previous studies have demonstrated significant differences in adult cardiometabolic indices between groups of infants with rapid vs slow weight gain in the first 3–6 months after birth [49] using data from 65 and 22 adults, respectively. A conservative 0.5 change in z-score between metformin-exposed and non-exposed infants (at each time point) will therefore represent a robust and important clinical difference. Covariates (maternal glycaemic control, infant feeding, birthweight z-score and infant height) likely to be associated with the primary outcome will be included in the adjusted analysis to improve the precision of the treatment effect as appropriate. This will be balanced against the loss of effective sample size through use of degrees of freedom following inclusion of covariates [50].

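### MIMICH II's primary infant contrast uses only infants weighed at 12 months, with optional adjustment for post-randomisation birthweight; birth and 3–6-month weights of infants lost later go unused, and arm-differential return could bias it

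*Protocol article*

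**What the plan says.** All references are to the protocol article.

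- **Outcome (Outcomes for MIMICH II).** The primary infant outcome is "Difference in the delta (birth to visit 2) weight SD score between infants following maternal treatment with or without metformin". The sample size section identifies the end point as 12 months of age.
- **Size (Sample size considerations {14}).** The section gives 39 per group for one power level and 70 for a higher one, labelled as beta 0.8 and 0.9. The inputs are "Assuming a population z-score weight gain of 0.08–0.12 (SD 0.9") and a difference of 0.5. The section states that these numbers "per group will be required to show a 0.5 difference in z-score between groups (retention 35–63" per cent).
- **Adjustment (same section).** Maternal glycaemic control, infant feeding, birthweight z-score and infant height may be added as covariates, for precision and as appropriate.
- **Entry (Trial setting {9}).** "Participation in the postnatal follow-up study will be offered to participants who consent to be contacted about future research". Consent for MIMICH II is separate, the preceding trial is open-label, and section {18b} makes women who discontinue or withdraw from MIMICH ineligible.
- **Birth data.** Section {18b} still collects birth details after discontinuation, and section {14} puts MIMICH dropout at 10%.
- **Missing data (sections {20a} and {20c}).** Observed outcome data are analysed, and the amount of and reasons for missingness are reported. No other method is named.

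**The concern.** The primary contrast is one two-point change, so an infant without a 12-month weight contributes nothing to it. This holds even when the trial has the infant's arm, birthweight and 3–6-month weight. A 10% loss could be handled by reporting missingness. Here the stated sample size is met with more than a third of the randomised cohort absent, and entry depends on a further choice by mothers who know their allocation.

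Two things are at stake. First, if return depends on infant size or growth differently in the two arms, the difference among attenders is not the difference among all infants born in the trial. Second, the planned covariate does not repair this. Birthweight comes after randomisation, and MIMICH itself is designed to detect a treatment effect on growth up to birth. Adjusting for birthweight therefore removes any effect on later gain that runs through birthweight, and so changes the quantity estimated.

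**Working it through.** **1. The plan's retention figures.** The abstract recruits "in a target sample of 225 participants", allocated 1:1.

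- 2 × 39 / 225 = 78/225 = 34.7%
- 2 × 70 / 225 = 140/225 = 62.2%

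These reproduce the stated range to within a point.

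**2. The plan's sample sizes.** n per group = 2 × (SD/difference)² × (z for alpha + z for power)². Two-sided 0.05 is assumed. Alpha is not stated for MIMICH II, but the same convention gives 94–95 per arm for MIMICH, matching "A sample size of 190 women (95 in each group) will provide 80% power".

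- 80%: 2 × (0.9/0.5)² × (1.960 + 0.842)² = 50.9, so 51 (52 with the t distribution)
- 90%: 2 × (0.9/0.5)² × (1.960 + 1.282)² = 68.1, so 69 (70 with t)

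The figure of 70 reproduces; 39 does not. Power at 39 per group is about 0.69. One-sided 0.05 gives 41 and 56, so no single convention gives both figures. With 51 per group the required retention is 102/225 = 45%, and the range becomes about 45–63%.

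**3. How large selection bias could be.** Bias in an arm = (1 − retention) × (attender mean − non-attender mean). For a bias of 0.25 z, half the target, the attender/non-attender gap must differ between arms by 0.25/(1 − 0.453) = 0.46 z at 45% retention and 0.25/(1 − 0.622) = 0.66 z at 62%.

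With SD 0.9 and logistic attendance depending on weight gain in one arm only (slopes assumed):

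| Retention | Slope 0.3 per SD (odds × 1.35) | Slope 0.5 per SD (odds × 1.65) |
|---|---|---|
| 45% | 0.15 z | 0.23 z |
| 63% | 0.10 z | 0.16 z |

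Identical selection with equal retention gives zero. In a threshold-selection model, the same mechanism in both arms (correlation 0.3 between return and gain) with 35% v 63% retention gives 0.12 z.

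**4. What the birthweight covariate does.** Assumed example: arm shift in birthweight z of 0.41 (borrowed from the MIMICH target), correlation of birthweight with later gain −0.4, SD of gain 0.9, and no other treatment effect. The true arm difference in gain is 0.9 × (−0.4) × 0.41 = −0.15. Return depends on birthweight in one arm (log-odds slope +0.5 or −0.5 per SD), with 45% retention:

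| Analysis | Slope +0.5 | Slope −0.5 |
|---|---|---|
| Attenders, unadjusted | −0.24 | −0.05 |
| Attenders, adjusted for birthweight | 0.00 | 0.00 |
| Regression within arm, averaged over all infants with a birthweight | −0.15 | −0.15 |

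The zero in the second row follows from the construction, since the whole effect runs through birthweight. It shows that the adjusted contrast answers a different question. The third row uses the birth data of non-attenders, as a likelihood model of all the weights would.

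**5. The limit of using birth data.** If return depends on the later gain itself in one arm (correlation 0.3), conditioning on birthweight leaves 0.24 of a 0.29 z bias at 35% retention and 0.14 of 0.16 z at 63%. Birth data alone do not solve that case.

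**The case against.** Several stronger readings are tempting, and the document does not support them.

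- **That the plan expects to lose 37–65% of infants.** It does not. The percentages are what the stated numbers require. The recruitment section lists measures to encourage attendance, and actual return may be higher.
- **That low retention by itself biases the result.** It does not. Return must differ by arm, in mechanism or in rate, and nothing in the article shows that it will. The slopes above are assumptions.
- **That selection could account for most of the 0.5 target.** At the corrected 45% the assumed slopes give at most 0.23 z. Larger values arise at 35%, which rests on the unsupported 39 per group, or under stronger selection.
- **That a missing-data method is absent.** The analysis plan is not shown and may contain one. The observed-data wording also sits beside text specific to MIMICH. The fair point is what the article does state: a two-point change, observed data, and a possible birthweight covariate.

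A further defence is that adjusting for birthweight removes bias when return depends on birthweight. That holds for the effect at a given birthweight, but not for the arm difference in change named as the outcome.

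The article also calls MIMICH II observational, and its outcome wording could mean treatment received. Even so, the groups come from a randomised trial, and the value of the comparison lies in keeping them. Finally, 3–6-month weights are not wholly unused, because the 0.5 difference is set at each time point. They do not, however, inform the birth-to-12-month contrast.

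**Conclusion.** The point stands in limited form and should be dealt with before analysis. The stated primary infant analysis discards birth and 3–6-month weights of infants without a 12-month weight. Its optional adjustment changes the estimand. It is also open to bias if return differs by arm: about 0.15–0.23 z at 45% retention and 0.10–0.16 z at 63%, or roughly 20–47% of the 0.5 target. These sizes rest on SD 0.9, selection in one arm only and the assumed slopes. With like selection and equal retention the bias is nil. The lower end of the stated retention range also needs correcting, from 35% to about 45%, if 80% power is intended.

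**What to change.** 1. Make the primary infant analysis a mixed model of weight z-score at birth, 3–6 months and 12 months, by randomised arm, in all infants of randomised women with at least one weight. Take the arm difference in change from birth to 12 months. Leave birthweight z-score out as a covariate, since it is one of the modelled outcomes.
2. Tabulate baseline and birth data of attenders and non-attenders by arm.
3. Add two sensitivity analyses: weighting attenders by the inverse probability of attendance, and a delta-adjusted analysis that lets non-attenders' growth differ from the model's prediction. The second is needed because neither the mixed model nor the weighting fully corrects return driven by later growth itself.
4. Restate the sample size for 80% power as 51–52 per group with about 45% retention, and label the values as power.

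The cost is analysis-plan wording and modest extra analysis, with no new visits or data. The main model relies on data being missing at random given what was collected.

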The MiTy trial, which showed an association with SGA in the metformin-treated group, recently published data about the infants of these mothers at 2 years and found their anthropometric measures were similar between groups at the 2-year endpoint, but that metformin-exposed male infants had a different growth trajectory, and that BMI was higher from 6 to 24 months [34]. Postnatal catch-up or accelerated growth often defined as a delta weight SD score > 0.5 or 0.67 has been consistently associated with insulin resistance and metabolic syndrome-related disorders (e.g. type 2 diabetes) in later life [35–37]. Accelerated growth during early postnatal life, irrespective of birth weight, has been shown to associate with changes in β-cell function at 12 months [38, 39] and appears to be particularly important for metabolic health in later life [40]. It is unclear from existing studies whether metformin exposure in utero affects postnatal catch-up and therefore impacts future cardiometabolic health in later life. Of note, infants exposed to metformin in the EMPOWaR study [41], a randomised study of obese pregnant women, were thinner (lower ponderal index) at birth, which, if associated with accelerated postnatal weight gain (akin to the mouse studies), could confer an increased cardiometabolic risk to the offspring [42].

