### Plans to promote participant retention and complete follow-up {18b}

All recruits will receive continuity of care in the specialist research clinic to encourage participation and retention. Confirmation of a willingness to continue in the trial will be confirmed at each clinical/study visit. Participants who choose to end their participation in the MIMICH trial but consent to the collection of birth and outcome data will be classed as discontinuations. In this case, no further data during antenatal care will be collected, but maternal, neonatal and birth details will be collected. Participants who end their participation and decline collection of their birth and outcome data will be classed as withdrawals. In this case, all data collection from the point of withdrawal will cease. Participants who discontinue or withdraw from MIMICH will not be eligible for MIMICH II. Participants who deviate from their allocated treatment arm will continue in the study, with treatment exposure recorded at each visit.

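### MIMICH II plans to adjust infant weight gain for birthweight, infant height, feeding and glycaemic control, which arise after randomisation, and does not say that infants are grouped as allocated

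*Protocol article*

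**What the plan says.** The sample size section {14} defines the follow-up outcome as "weight gain trajectory, determined as change in weight z-score, between birth and 12 months of age" and then gives the analysis: "Covariates (maternal glycaemic control, infant feeding, birthweight z-score and infant height) likely to be associated with the primary outcome will be included". The section calls this the adjusted analysis, gives better precision as its purpose, and leaves its use to be decided as suits. It adds that the gain will be weighed against the degrees of freedom used.

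The contrast is worded in two ways. The MIMICH II outcome list compares weight change "between infants following maternal treatment with or without metformin". The sample size section justifies its 0.5 z-score difference as one "between metformin-exposed and non-exposed infants". Neither says whether infants are grouped by the arm their mother was allocated to or by what she took.

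The scientific question is in the postnatal background section: "It is unclear from existing studies whether metformin exposure in utero affects postnatal catch-up".

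**The concern.** Covariate adjustment in a randomised comparison is harmless, and usually helpful, when the covariates are fixed before randomisation. The four listed here are not, and the treatment may move each of them. Conditioning on such a variable changes the quantity being estimated. Birthweight is the clearest case. If metformin lowers birthweight and smaller infants then gain faster, that gain is part of the effect MIMICH II sets out to measure, and a model that holds birthweight fixed takes it out. Holding infant height fixed moves the outcome from weight gain towards weight-for-length.

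At stake is whether the follow-up reports the total effect of the treatment policy on infant growth or a conditional effect that is harder to interpret. If groups were also formed by exposure, the comparison would lose the protection of randomisation.

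**Working it through.** **1. Timing and status of each covariate.** Randomisation is at 6+0 to 30+0 weeks (Eligibility {10}; Sequence generation {16a}).

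| Covariate | When it arises | How the article treats it elsewhere |
|---|---|---|
| Birthweight z-score | At birth | Neonatal outcome; end point of MIMICH's primary outcome; the sample size text expects withholding metformin to move it; the subtracted term in the MIMICH II outcome |
| Infant height | After birth | Crown-heel length is an infant secondary outcome; the background cites exposed children being taller at 18 months |
| Infant feeding | After birth | Breastfeeding at discharge is a neonatal outcome |
| Maternal glycaemic control | At least partly after randomisation (no time point given) | Outcomes {12} uses it as a marker of treatment effect |

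None is clearly a pre-randomisation variable.

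**2. What adjusting for birthweight does.** Let BW be birthweight z-score, W the 12-month weight z-score, A = 1 for metformin, d the fall in BW caused by metformin, b the carry-over of BW into W, and τ any effect on W not passing through BW:

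- BW = −d·A + error
- W = b·BW + τ·A + error
- delta = W − BW

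The total effect of A on delta is τ + (1 − b)·d. With BW in the model, the coefficient of A is τ. The outcome could then equally be W, because subtracting a covariate from the outcome leaves the treatment coefficient unchanged. The term (1 − b)·d, which is catch-up through birthweight, disappears; τ remains.

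**3. Size.** The inputs from section {14} are the birthweight difference of −0.28 (−0.45 to −0.10) in the cited trial of metformin in type 2 diabetes, MIMICH's design difference of 0.41, and the MIMICH II target of 0.5. The 0.41 is a difference in change from second trimester to birth; using it for d assumes no difference at the second-trimester scans. The article gives no value for b. I assume 0.2 to 0.7, so 1 − b is 0.3 to 0.8.

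| d | (1 − b)·d | Share of 0.5 |
|---|---|---|
| 0.10 | 0.03 to 0.08 | 6% to 16% |
| 0.28 | 0.084 to 0.224 | 17% to 45% |
| 0.41 | 0.123 to 0.328 | 25% to 66% |
| 0.45 | 0.135 to 0.36 | 27% to 72% |

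Simulation with 1,000,000 infants, b = 0.4 and d = 0.28 agrees:

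- τ = 0: unadjusted 0.17, adjusted 0.00 (formula 0.6 × 0.28 = 0.168 and 0).
- τ = 0.20: unadjusted 0.37, adjusted 0.20 (formula 0.20 + 0.168 = 0.368 and 0.20).

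**4. Added bias.** Now let an unmeasured factor act on both BW and W with coefficient 0.5 each, total BW variance 1 within arm, and τ = 0. The slope of W on BW within arm becomes 0.4 + 0.5 × 0.5 = 0.65. The adjusted coefficient of A is (0.65 − 0.4) × 0.28 = 0.07 (simulated 0.071), although the true direct effect is 0 and the total effect is 0.17. The adjusted figure then estimates neither.

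**5. Grouping.** Section {11b} expects some women in the intervention arm to take metformin and some in usual care not to tolerate it. Under {11a}, metformin starts only when diet and lifestyle do not meet targets, so some usual-care women may never start. Allocated and exposed groups will therefore differ. Section {20a} makes intention to treat the main analysis for primary and secondary outcomes, but the model it gives is for foetal growth only and MIMICH II is not mentioned. Trial design {8} calls MIMICH II an observational cohort.

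**6. The plan's own sample size.** With difference 0.5, SD 0.9 and two-sided 5% (assumed, as none is stated), 90% power needs 69 per group against the stated 70. For 80% power, 51 are needed against the stated 39. That second mismatch is a separate matter and this point does not depend on it.

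**The case against.** Several stronger readings are tempting, and the article does not support them.

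- **That this is the primary model.** A reader might infer it. The text speaks only of an adjusted analysis, used as appropriate. Section {14} has near-identical wording for MIMICH itself, naming mean daily glucose and time in target, yet the MIMICH model in {20a} adjusts for baseline z-score and minimisation variables and has no glucose term. A by-arm main analysis of MIMICH II is therefore not ruled out. What remains is that no other MIMICH II model is described.
- **That the catch-up effect is wholly blocked.** Only the part through birthweight, length, feeding or glycaemia is affected; a direct effect survives, as step 2 shows. The background also raises a birthweight-conditional question, citing accelerated early growth as harmful whatever the birthweight. That could justify a conditional model as a stated secondary question, but not as a gain in precision.
- **That the randomised comparison is abandoned.** The wording in the outcome list echoes how {6b} describes the randomised comparators, and the exposed/non-exposed phrase justifies an effect size rather than defining analysis groups. Section {20b} makes treatment received exploratory, though for foetal growth. The text is ambiguous; it does not choose an as-treated analysis.
- **That birthweight is simply the baseline of a change score.** It is the baseline for the infant visits, but treatment precedes it, so the usual argument for baseline adjustment does not carry over.

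A reader might also link this to the rule "Participants who discontinue or withdraw from MIMICH will not be eligible for MIMICH II". That concerns selection into the cohort. Under {18b}, women who deviate from allocated treatment stay in the study, and the documents give no figure for the effect of the rule. It is a separate question and forms no part of this point.

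**Conclusion.** The point holds in limited form. The article fixes a list of post-randomisation covariates under a precision rationale that does not fit them, and leaves open whether infants are compared as allocated. Followed as written, the adjusted model estimates an effect at fixed birthweight and length, drops the birthweight-mediated part of catch-up, and may add bias.

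The timing argument rests on the article alone. The size does not. The 0.08 to 0.22 z for a birthweight effect of 0.28 depends on the assumed carry-over of 0.2 to 0.7 and a linear model, and the common-cause example on assumed coefficients of 0.5. These figures show that the loss could be material against a 0.5 z target; they do not predict it. Whether the main result is affected depends on an analysis plan that is not shown.

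**What to change.** State that the primary MIMICH II analysis compares delta weight z-score by allocated arm, adjusted only for the minimisation factors and other covariates measured before randomisation. A glycaemic measure taken before randomisation could be among them. Replace the exposure wording with allocated arm wherever the primary contrast is described. Label any model with birthweight z-score, infant height, feeding, post-randomisation glycaemic control or actual metformin exposure as exploratory, and say what each one estimates.

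The cost is a change of wording and slightly less apparent precision, since birthweight and height predict weight gain. The stated sample size does not visibly rely on that precision: the SD of 0.9 is given for population weight gain, with no reduction for covariates mentioned.
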